**Figure 1 figure1:**
[figure not shown]
Architectural diagram of the Mental Health Intelligent Information Resource Assistant (MIRA) chatbot and resource portal system. API: application programming interface; REST: Representational State Transfer.

Of importance is the use of both NLP (via text-based entry) and decision trees (rule-based responses based on the use of predetermined button options) to support response generation. Most chatbots in mental health use either one or the other, whereas MIRA uses a hybrid approach to enhance functionality and end-user experience by offering them the choice or control to use both interchangeably during their exchange with MIRA. It is our understanding at the time of writing this paper that this approach in itself (using NLP and rule-based responses and allowing users to control the conversation) is a novel application of AI within the mental health field [58].

The chatbot was built to associate various terms or phrases as being of an urgent or serious nature and has been prompted to immediately provide information on emergency services should this association be triggered. For example, if the client indicates that they are experiencing suicidal thoughts, the chatbot will immediately provide them with emergency contact information and the Crisis Services Canada phone number, chat line, and texting information. This emergency response was flagged by mental health experts on our team and our Expert Advisory Committee as being of critical importance in supporting individuals experiencing urgent mental health–related challenges. Hypothetical phrases used for baseline training data were developed with the assistance of these members as well.

Following this work, our computing science team members worked on the incorporation of data augmentation (ie, the use of an AI algorithm that, using existing examples and hypothetical questions, can create new variations of hypothetical questions that could be asked to further refine chatbot functionality) as well as web browser automation via the Selenium platform to test chatbot functionality to mimic anticipated and unanticipated client questions, responses, and behaviors. Over 20 different data augmentation algorithms were used, including contextual word embeddings, random character errors, and synonym augmentations. Stanford’s CoreNLP (Stanford NLP Group), an open-source NLP tool, will be used to further enhance entity extraction [73].

The two main purposes of MIRA are to provide individuals with (1) information or education on substance use and mental illnesses generally (simple educational information including general definitions and descriptions of symptoms written at a lay audience level) and (2) information on services and programs in Canada or, if voluntarily provided, in the specific city or village, region, or province of the identified end user. The level of specificity of the information, services, or programs provided is dependent on the level of information voluntarily shared by the client. For example, the client may ask for a definition of mood disorders or, alternatively, for an in-person group therapy program for individuals managing major depressive disorder in Edmonton, Alberta. The programming of these 2 components requires different approaches, as detailed below.

The education resource component of the chatbot was developed by first identifying common mental health ailments or challenges. A list of psychiatric disorders was extracted from the Diagnostic and Statistical Manual of Mental Disorders by a psychiatry expert on the team, who then extracted common language used on the web by reputable (known government and not-for-profit, government-supported) organizations whose websites were tailored to a lay audience and linked clinical and common language. This linking was helpful both to train the chatbot on relationships between lexicons used in the psychiatric field and audiences and to serve as a preliminary list of common ailments. Following the development of these lists, volunteers at the MDSC supported the collection of web-based resources that provided the following information on each specific ailment: definition of the disorder or ailment, list of associated symptoms, and a description of common associated treatments. These web-based resources and their relevant informational data were individually logged in the MIRA portal (MIRA portal details outlined below) and subject to review by a 30-member Expert Advisory Committee.

The service and program resource component was developed by first logging a resource list provided on the MDSC website. The act of logging was conducted by MDSC volunteers. Following this, government websites were reviewed by team members and volunteers for additional resource lists. Where lists of recommended resources were provided, volunteers were asked to log these resources. These web-based resources were also subject to review by a 30-member Expert Advisory Committee. The MIRA portal currently has >750 fully vetted resources.

#### Testing MIRA

The MIRA core team collaboratively determined a quality threshold for the release of a minimum viable chatbot prototype based on a variety of performance metrics. Performance measures, including accuracy of intent recognition and entity extraction as well as average rending time, were used by the computing science team to monitor the progress of chatbot training and refinement. Where needed, the team strategically addressed particular elements of the chatbot that they felt may enhance measures reporting lower than acceptable metrics.

The chatbot was in alpha testing from December 2021 to February 2022. The chatbot was then beta tested by members of our 30-member, multidisciplinary Expert Advisory Committee from February 7, 2022, to May 1, 2022. Comments were logged, and changes were made to the chatbot in real time. Testing was enhanced using automation via Selenium, a web browser automation tool, to repeatedly test anticipated end-user behavior and log programming bugs and errors.

The chatbot was launched for the pilot population on May 2, 2022. Data collection is anticipated to take place from May 2, 2022, to May 2, 2023. The publication of a preliminary synthesis of the results will be sought in spring or summer 2022, followed by a more comprehensive evaluation in spring 2023.

#### Interacting With MIRA

Once the client clicks on the MIRA URL [74], they are directed to a webpage with the MIRA chatbot interface. MIRA begins by welcoming the client and asks them for their consent to use anonymized data from the conversation to evaluate and improve its services, with a link to a pop-up with consent information (Multimedia Appendix 2). If the client provides consent, the chatbot then asks a short series of demographic-related questions—employment type, location, and end user (eg, for the client or for someone else; if *someone else*, then the age of the end user is also collected; Multimedia Appendix 3). Following these preliminary questions, the chatbot asks in an open-ended manner (eg, “How can I help you?”) and provides some examples of questions that could be asked in the form of button options (eg, “I want to find programs and services” or “I want to learn coping skills”; Multimedia Appendix 4). If a client asks to “chat” with MIRA or begins expressing feelings opposed to an obvious request for information, eEliza programming will be prompted (Multimedia Appendix 5). The MIRA website, MIRA chatbot, and MIRA Resource Portal (renamed the MIRA Resource Library for the May 2 launch) were tested for compatibility with multiple electronic devices, including tablets, smartphones, and desktop computers, as well as multiple browser applications, including Safari and Chrome.

#### The MIRA Portal

The internet may contain information with inaccurate content, bias, and insufficient evidence [75,76]. This is why MIRA does not draw resource recommendations via the open internet and, instead, provides resource recommendations drawn from the MIRA Resource Portal. The MIRA Resource Portal is a resource repository in which MDSC volunteers have cataloged and annotated metadata of >750 resources to date. These resources were assessed for quality by a 30-member Expert Advisory Committee using an approach reflecting the academic peer-review process. More specifically, resources were assigned to committee members by an editor (the study coordinator). Each resource was subject to review by at least two different reviewers. Reviewers were guided by an evaluation matrix developed using a hybrid of items that were drawn from existing validated tools [75,77,78]. The factors assessed included (1) readability, (2) accessibility, and (3) quality [75,77,78]. This hybrid approach was taken as our definition of *resource* was broad (see the *Resource Types* section) and included many types of resources (eg, phone number, website links, videos, audio recordings, images, and apps) and, as such, to our knowledge, no validated tool existed at the time of writing this paper. To date, >1600 resource reviews have been conducted, resulting in 750 resources that have been fully vetted and approved by the Expert Advisory Committee and are now accessible by the chatbot.

For the purposes of this study, *resource* is defined as evidence-supported, relevant, and reliable information that would satisfy an end user of the chatbot in retrieving general mental health information or connecting with the appropriate mental health services for their identified needs and circumstances. A recommended resource can be provided at the end of a dialogue as the final outcome or at any time during the exchange.

#### Resource Types

The types of resources included in the MIRA Resource Portal are shown in Textbox 1.

Types of resources included in the Mental Health Intelligent Information Resource Assistant Resource Portal.
**Resource types**
Health system navigation: information that connects clients with programs and services—includes a textual description of the resource and any of the elements of a typical contact record (email address, phone number, physical address of in-person service, hours of operation, and URL if it is a website)Informational or education reference: includes a textual description of the resource and the website URL or the URL to an audio, video, image, or PDF attachmentSimple answer: just a textual description that can be provided as an answer to a direct factual question

If a resource received a mixed review, it was then subject to review by a third reviewer (a tiebreaker who was also a member of the Expert Advisory Committee). Reviews were made anonymous to everyone with the exception of the editor, who was responsible for assigning resources, to allow reviewers to be candid, and all reviewers were asked to acknowledge any conflicts of interest before being permitted to review a resource. See Figure 1 for an architectural diagram of the MIRA chatbot and portal system.

### Participants

For the purposes of this project, the definition of the target sample was broadened to capture all health-related personnel and their respective families who may be affected by heightened mental health burden in light of the ongoing pandemic. In addition, direct or vicarious trauma or psychological distress in a health care environment is not limited to medical staff [79,80]. Therefore, *health care worker* will be defined as outlined in Textbox 2.

Definition of *health worker* for this study.
***Health worker* definition**
“Any health professionals and any staff member, contract worker, student or trainee, registered volunteer, or other essential caregiver currently working in a healthcare organization, including workers that are not providing direct patient care and are frequently in the patient environment. This includes cleaning staff, food services staff, information technology staff, security, research staff, and other administrative staff.Workers providing healthcare service or direct patient service in a congregate, residential or community setting outside of a healthcare organization (e.g., nurse providing patient care in a school, worker performing personal support services in an assisted living facility, medical first responder in the community, peer worker in a shelter)” [81].

The definition of health care worker varies considerably by health authority or administrator. As such, the following numbers were used to determine a general goal post for a target sample size recognizing that the data sources (Alberta Health Services and Nova Scotia Health Authority) may have differing inclusion criteria for what is categorized as a health care worker. There are approximately 240,000 frontline Alberta Health Services workers in Alberta [82], and there are 23,400 health care workers in Nova Scotia [83]. To include family members into sample size calculations, 2011 Statistics Canada estimates on the average number of individuals in a household were used (2.5 per household) [84]. With a 95% CI and 3% margin of error, the sample size target was estimated to be 1066 for Alberta and 1048 for Nova Scotia. More specifically, this sample size refers to the number of participants who consent to using the chatbot. This study will seek to slightly oversample from each province (Alberta: n=1100; Nova Scotia: n=1100). In reflection of the general experiences of other researchers with participation rates for web-based surveys (34%-43% [85-89]), we will aim to collect between 374 and 473 partial and complete baseline surveys and 110 partial and complete follow-up surveys per province. To the authors’ knowledge at the time of writing this paper, this study is the first to evaluate the use of conversational agents or chatbots to support mental health system navigation; as such, the effect size is unknown at the time of the design phase of the study, and power analysis will need to be conducted as the study team actively gathers data to ensure that our sample size is adequate. Therefore, the sample size is subject to re-estimation during the course of this study.

Participant recruitment will be conducted through snowball sampling via word of mouth, social media advertisements, physical advertisements (study posters and study information posted on physical bulletin boards in hospital staff rooms as well as in newsletters to staff where possible), and referrals via our network and partners (including medical professional organizations). After consenting to take part in the study via a web-based consent form, the participants will be asked if they would like to take part in voluntary follow-up surveys following the use of the chatbot. Regardless of their response, they will then be able to immediately engage with the chatbot. The inclusion criteria are being aged >18 years at the start of the study, being a health care worker or a family member of a health care worker, being located in Alberta or Nova Scotia, being able to speak and read English, and having access to the internet. The chatbot will be developed with the option of adding French and other languages of peoples geographically located within the settlement of Canada in future iterations of the chatbot (eg, Cree, Inuktitut, and Ojibway). The exclusion criteria are individuals aged <18 years, individuals in provinces outside Alberta and Nova Scotia, those with limited comprehension of English, and those without internet access. However, if a client tries to access this service to support an individual aged <18 years or outside the 2 provinces indicated, the chatbot will include cross-Canadian resources that could support them.

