### Chatbot Development

#### A Multidisciplinary Team

In recognition of the complex nature of developing and implementing accepted and effective state-of-the-art computing science technologies seeking to support mental health and wellness within the public health domain, a multidisciplinary team is required.

The MIRA Operational Team (including senior leadership, fellows, students, and support staff) and voluntary Expert Advisory Committee include computing science and psychiatry experts, health care workers, and family members and individuals with lived experience. To develop a new technology that is accessible to all Canadians and does not perpetuate the systemic racism inherent within the public health system, MIRA is being cocreated with the Indigenous community and includes an ethnically and culturally diverse team leading and supporting its development from tip to tail. See Multimedia Appendix 1 for a graphical description of this multidisciplinary approach.

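### The eligibility criteria do not keep people who built, tested, logged or vetted MIRA out of the sample that judges it

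*Protocol article*

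**What the plan says.** **Eligibility (Methods, Participants).** The role criterion is "being a health care worker or a family member of a health care worker, being located in Alberta or Nova Scotia". The exclusion list reads "The exclusion criteria are individuals aged <18 years, individuals in provinces outside Alberta and Nova Scotia, those with limited comprehension of English", and ends with lack of internet access. The health worker definition is broad and takes in "information technology staff, security, research staff, and other administrative staff".

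**Who made and checked MIRA.** Under A Multidisciplinary Team, the Operational Team and the "voluntary Expert Advisory Committee include computing science and psychiatry experts, health care workers, and family members and individuals with lived experience". Under Testing MIRA, the chatbot was "beta tested by members of our 30-member, multidisciplinary Expert Advisory Committee from February 7, 2022, to May 1, 2022", and it was launched on May 2, 2022. Under The MIRA Portal, the chatbot draws only on the portal, which holds "750 resources that have been fully vetted and approved by the Expert Advisory Committee". Volunteers of a partner organization logged the resources.

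**Recruitment.** Among several parallel channels (snowball sampling, social media, posters, newsletters), the Participants section names "referrals via our network and partners (including medical professional organizations"). The Limitations section acknowledges possible selection bias from using the research team's network and affiliated organizations, and responds by adding recruitment channels.

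**Primary outcome (Outcome Evaluation).** Success is a respondent's yes to two survey questions: whether the recommended resources were appropriate, and whether the respondent followed up or connected with them. The minimum threshold is >50%.

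**Identification.** The entry questions under Interacting With MIRA cover employment type, location and end user. Under Procedures, chatbot use is anonymous, and survey emails are deleted once the two surveys are linked.

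**The concern.** The study asks whether health care workers and their families are connected with appropriate resources. A committee member who is a health care worker in either province meets every listed criterion. Such a person may have spent up to 12 weeks testing the chatbot (February 7 to May 1, 2022, is 84 days), with launch the next day, and has a stake in how it performs. The primary outcome rests wholly on self-report, and so do the trust and acceptability items.

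The article recognises this kind of conflict at the vetting stage, where reviewers had to acknowledge conflicts of interest before reviewing a resource. It describes no matching safeguard for respondents. More recruitment channels dilute insiders without removing them. The measures against response bias (oversampling, anonymity, validated items, census weighting) do not bear on them either.

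At stake is the reading of a result near 50%. If some respondents helped to make the tool and cannot be told apart, such a result cannot be cleanly attributed to ordinary users.

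**Working it through.** **1. The article's own figures.** The precision formula is n0 = z²p(1−p)/e², with z = 1.95996, e = 0.03 and p = 0.5 (p is assumed, as it is not stated). It gives n0 = 1067.07. The finite population correction is n = n0/(1 + (n0−1)/N).
- Alberta: N = 240,000 × 2.5 = 600,000, so n = 1065.18, rounded up to 1066.
- Nova Scotia: N = 23,400 × 2.5 = 58,500, so n = 1047.97, rounded up to 1048.

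Both match the article. The survey goals also reproduce: 34% and 43% of 1100 are 374 and 473, and 110 is 10% of 1100. No stated figure is wrong; the point concerns who is counted.

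**2. Effect of insiders on the observed rate.** Let n be the respondents, k the insiders among them, p the success rate of the others, and r the success rate of insiders. Then observed rate = [k·r + (n−k)·p]/n, and shift = (k/n)(r − p). Neither k, p nor r is given in the documents.

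**3. Illustration with p = 0.45 and r = 1.**

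| n | k | Observed rate |
|---|---|---|
| 110 | 5 | (5 + 105 × 0.45)/110 = 47.5% |
| 110 | 10 | (10 + 100 × 0.45)/110 = 50.0% |
| 110 | 11 | (11 + 99 × 0.45)/110 = 50.5% |
| 110 | 15 | (15 + 95 × 0.45)/110 = 52.5% |
| 220 | 5 | (5 + 215 × 0.45)/220 = 46.25% |
| 220 | 20 | (20 + 200 × 0.45)/220 = 50.0% |
| 220 | 21 | (21 + 199 × 0.45)/220 = 50.25% |

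The threshold is strictly above 50%, so 10 of 110 and 20 of 220 only reach it; 11 and 21 pass it. Five of 220 shift the rate by 1.25 points.

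**4. Chance of exceeding 50%** on the same assumptions, with outsiders binomial. At n = 110 (at least 56 successes) it is 12.5% with no insiders, 26.1% with 5, 45.9% with 10 and 67.8% with 15. At n = 220 (at least 111) it is 6.0%, 11.5%, 20.2% and 32.3%.

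**5. Sensitivity to the assumptions.**
- Outsider rate 40%: passing needs k > n(0.5 − p)/(1 − p). That is 110 × 0.10/0.60 = 18.3, so 19 insiders, or 36.7, so 37, when pooled. The latter exceeds the whole 30-member committee.
- Insiders who all answer no to connection (r = 0), with p = 0.45: 11 of 110 lower the rate to 99 × 0.45/110 = 40.5%.
- Larger denominator: with 374 respondents, 10 insiders give (10 + 364 × 0.45)/374 = 46.5%.
- Engagement measures on about 2200 consenting users: all 30 committee members would be 30/2200 = 1.4%.

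**The case against.** The case on the other side has several parts, and much of it stands.

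- **Silence in a condensed article.** A full protocol or ethics file could exclude study personnel. That is possible. But the article sets out its inclusion and exclusion criteria as explicit lists, so eligibility is something it fixes and does not leave elsewhere.
- **The pool is smaller than it looks.** This stands. The team is pan-Canadian, so not every member is in the two provinces. The family members on the committee are not said to be families of health care workers, and the partner's volunteers are not said to work in a healthcare organization. The eligible number is unknown.
- **Members would not be rating resources that they approved themselves.** Largely right. Each resource went to at least two reviewers, not to the whole committee. About 1600 reviews over 30 members is some 53 each if evenly spread, or 7% of 750. The conflict lies in their stake in MIRA and prior exposure to it more than in any single resource.
- **Direction.** A reader might infer that insiders must inflate the primary outcome. The documents do not show this: an insider with no current need could truthfully answer no on connection.
- **Later removal is possible.** A reader might also infer that insiders can never be removed. For surveys this is too strong, since registered emails exist until linkage and could be matched to team lists before deletion. The plan does not provide for it, and it would not reach the anonymous chatbot data.
- **The denominator may be larger.** Participants uses the term follow-up surveys for both questionnaires, so the primary analysis could draw on 374 to 473 per province, which weakens the effect.

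**Conclusion.** The point holds as a gap in eligibility, not as a demonstrated bias. As written, the criteria admit adult health care workers in Alberta or Nova Scotia who built, tested, logged or vetted MIRA. Recruitment can reach them, and no described entry question would flag them.

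The size is unknown. The counts of 11 of 110 and 21 of 220 rest on two assumptions that the documents do not supply: 45% success among outsiders, just below the threshold, and a double yes from every insider. With fewer insiders, a larger denominator or a lower outsider rate, the effect is small or does not change the conclusion. The documents do not support reading the 30 committee members as 30 likely respondents.

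This is a cheap improvement to make, chiefly because separating these people afterwards is unreliable.

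**What to change.** 1. Add to the criteria in Participants an exclusion from the study sample for Operational Team and Expert Advisory Committee members, alpha or beta testers, and volunteers who logged or reviewed resources.
2. Add one yes/no item after consent, asking whether the person has helped to build, test or review MIRA or its resources.
3. Keep the chatbot open to those who answer yes, but leave them out of the sample count and of the primary, satisfaction and engagement analyses.
4. For any surveys collected before the item is in place, match registered emails against team, committee and volunteer lists before the emails are deleted.

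The cost is one line of text, one question and the loss of a small number of respondents. The sample size targets of 1066 and 1048 do not change.
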